## Abstract

Despite the myriad benefits associated with regular physical activity (PA), few American adults accrue sufficient weekly PA. Although “lack of time” is often cited as a correlate of physical inactivity, a growing body of evidence suggests that, perhaps more importantly, people allocate their leisure-time to activities they find more enjoyable than PA. These findings underscore the need to devise physical activities that will be chosen over other enjoyable, but less healthy, behavioral alternatives. As a first step in this direction, we designed a group social PA play program for adults, known as PlayFit. The overarching philosophy of PlayFit is that fun and enjoyment are among the most important influences on PA adherence. In PlayFit, traditional sport games are modified to fulfill basic psychological needs, in a non-competitive, and non-contact environment. We will randomize 280 sedentary adults 18–50 years of age to 12-months of PlayFit or traditional group exercise, matching the groups on intensity, frequency, and duration. The primary outcomes include cardiorespiratory fitness (VO_2peak_), group adherence, and group enjoyment. We hypothesize that, at 6 months, cardiorespiratory fitness will have increased to the same extent in both groups, but at 12 months, only those randomized to PlayFit will have maintained their fitness through better adherence than Group Exercise – and this outcome will be mediated by enjoyment of the assigned group. Findings from this study could provide evidence that a focus on providing fun and enjoyable PA experiences for adults may be a viable route toward improving PA adherence. A simple, inexpensive PA intervention, such as PlayFit, may represent one such approach to do so.

## Introduction

1

Fewer than 1-in-10 American adults meet weekly physical activity (PA) recommendations [1], greatly increasing their chances of developing cardiovascular disease, stroke, and other chronic medical conditions [2]. Despite enormous sums of money and intellectual energy poured into the issue of physical inactivity over the past three decades, little progress has been made in increasing population-level PA. Though adults often cite a variety of barriers to PA (e.g., lack of time, access [3]), a key and possibly modifiable barrier may be that many adults do not enjoy PA enough to participate regularly. For example, monthly gym memberships are used, on average, only once per week, despite the significant costs associated with maintaining membership, and this may be due in part to some individuals not enjoying traditional resistance training and/or machine-based exercises (e.g., treadmill, stationary bicycle) [4].

Given the growing body of evidence suggesting that people who perceive PA as pleasant and enjoyable are more likely to both adopt and adhere to physically active lifestyles [[5], [6], [7], [8], [9], [10], [11], [12], [13], [14], [15], [16]], some authors [7] recommend that PA “interventions should perhaps *initially focus* [emphases added] on increasing enjoyment of physical activity” followed by other known barriers. Furthermore, others [17,18] have suggested that traditional exercise prescriptions (i.e., those that focus primarily on participant safety and efficacy) could be rendered more effective by including an additional overarching consideration; specifically, whether the individual perceives the prescribed exercise to be pleasant and enjoyable. Williams and Evans proposed that repeated experiences of enjoyment during PA might perpetuate subsequent PA by leading to positive affective forecasts (i.e., whether the individual expects to feel good or bad) of subsequent PA [19]. Indeed, unless feelings related to the thought of being physically active are associated with pleasure and enjoyment, discovering the motivation to will oneself to engage in PA may be difficult in the midst of pleasant and enjoyable, but sedentary, alternatives (e.g., using a smartphone, reading or watching television) [[20], [21], [22], [23]].

Although several studies among younger children have attempted to increase exercise enjoyment [24], most of the extant work among adults has measured enjoyment responses to existing exercise regimens (e.g., high-intensity interval training versus moderate-intensity continuous exercise [25]), as opposed to directly comparing an established program (e.g., group exercise) to one matched on intensity, frequency, and duration but designed with the overarching philosophy of maximizing participant enjoyment. Moreover, few studies have investigated whether this primary focus on PA enjoyment would lead to better adherence, and, consequently, impart more health and fitness benefits. With this gap in mind, we began work to design a group PA program, known as PlayFit, specifically engineered to maximize enjoyment (see Table 1 for comparisons between PlayFit and recreational sport leagues) [26]. In PlayFit, we leverage several factors that are theorized to influence PA enjoyment, such as aspects of self-determination theory [27] and hedonic theory (i.e., pleasant experiences are more likely to be repeated [28]). The games of PlayFit are modified to make the games easier to play (i.e., to increase feelings of competence), allow for self-pacing and self-regulation of exercise intensity (i.e., to foster autonomy), and cultivate an environment conducive to positive social interactions (i.e., to improve feelings of relatedness). We hypothesize that the qualities of PlayFit could increase feelings of pleasure and perceived enjoyment of PA leading to a cycle of positive experiences that encourage PA adherence.

**Table 1 tbl1:** Features of PlayFit versus traditional adult sport leagues.

	PlayFit	Sport Leagues
Keeping score	No	Yes
Tracking standings	No	Yes
Static team membership	No	Yes
Single-sport	No	Yes
Player contact allowed	No	Yes
Official sport rules	No	Yes

## Methods

2

### Overview

2.1

The currently proposed study is a community-based, pragmatic randomized-controlled trial. The aims of this study are to 1) test the impact of PlayFit, compared to Small Team Training (STT; i.e., group exercise), on cardiorespiratory fitness (i.e., VO_2peak_) and moderate-to vigorous-intensity physical activity (MVPA; self-reported and objectively monitored) after 6-and 12-months, and 2) examine group differences in rates of injury and PA program enjoyment and changes in self-efficacy, blood pressure, loneliness, anxiety, and depression. We hypothesize that participants randomized to both groups will improve their cardiorespiratory fitness similarly at month-6 (i.e., approximately 3.5 ml/kg/min), but those randomized to PlayFit will maintain these increases at month-12 through better attendance. Additionally, we hypothesize that changes in group attendance and cardiorespiratory fitness at month-12 will be mediated by group enjoyment. Finally, we hypothesize that participants randomized to PlayFit will demonstrate greater improvements in indices of physical health (i.e., blood pressure) and mental health-related (i.e., anxiety) outcomes compared to STT while reporting similar injury rates. All study procedures presented here have been approved by the Institutional Review Board (IRB).

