### Sample size determination

4.1

Our power and sample size calculations are based on the following considerations. First, studies among untrained adults have shown that supervised group exercise can increase VO_2peak_ by approximately 4 ml/kg/min over 12 months [[64], [65], [66]]. Based on data derived from the National Health and Nutrition Examination Survey (NHANES) among men (*mean*_VO2peak_ = 42.1 ml/kg/minute) and women (*mean*_VO2peak_ = 34.2 ml/kg/minute) 30–39 years of age [67], we assume the baseline VO_2peak_ of participants will be approximately 35.0 (SD = 6.0). The SD of 6.0 is a conservative estimate using data from the Naval Research Lab, where it was 6.3 and 3.9 in men and women, respectively [68]. After 6-months, we anticipate that participants in both PlayFit and STT will improve their VO_2peak_ by approximately 10% (i.e., 3.5 ml/kg/min), owing to similar rates of program adherence. However, after 12-months, we anticipate only those randomized to PlayFit will maintain these changes in cardiorespiratory fitness, due to better program adherence. These differences in adherence will lead to a maintained improvement (versus baseline) in VO_2peak_ of PlayFit participants at 12-months of 3.5 ± 6.0 ml/kg/minute versus 1.0 ± 6.0 for STT. In this case, sample sizes of 112 in each group achieve 80% power to detect a mean difference of 2.5 ml/kg/minute with a standard deviation of 6.0 at the first time point, a standard deviation of 6.0 at the second time point, a two-sided significance level (*α*) of 0.05, and a correlation between measurements of 0.39. To account for participant attrition, we will oversample at a rate of 25%. Therefore, we will recruit up to 280 participants for the proposed study.

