#### Analysis of main outcome: fitness changes

4.1.3

To conduct these analyses using the principles of ITT, a slope will be fitted for the outcome variable (i.e., VO_2peak_) across each time point. Provided statistical assumptions are met, our hypotheses will be tested using random regression models [72,73]. Random regression models, also known as growth models, help to attenuate the impact of random data fluctuations, thereby increasing statistical power [72,74]. The use of random regression models also accounts for data non-independence, missing data, and nonlinear changes in the outcome variables [75].

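### Month-6 fitness gains and injury rates are hypothesised to be similar, but the only stated tests look for differences, and a non-significant result would not support similarity

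*Protocol article*

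**What the plan says.** The Abstract states as a hypothesis that "at 6 months, cardiorespiratory fitness will have increased to the same extent in both groups". The Overview (2.1) repeats it, with a size: "participants randomized to both groups will improve their cardiorespiratory fitness similarly at month-6 (i.e., approximately 3.5 ml/kg/min"). The same section adds a second similarity hypothesis, that PlayFit participants will do better on physical and mental health outcomes "while reporting similar injury rates".

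Sample size determination (4.1) uses the month-6 statement as a planning assumption: "participants in both PlayFit and STT will improve their VO_2peak_ by approximately 10% (i.e., 3.5 ml/kg/min"). The arms are then expected to part by month 12, at "3.5 ± 6.0 ml/kg/minute versus 1.0 ± 6.0 for STT". The calculation concerns that later gap only: "sample sizes of 112 in each group achieve 80% power to detect a mean difference of 2.5 ml/kg/minute", with SD 6.0 at each of two time points, correlation 0.39 and a two-sided 5% level.

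On testing, the section on the main outcome (4.1.3) says that "our hypotheses will be tested using random regression models". Section 4.1.4 uses the same models for the secondary outcomes. The article gives no margin, interval criterion or sample size for either similarity hypothesis.

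**The concern.** A hypothesis of no difference cannot be confirmed by a test whose null hypothesis is no difference. Failure to reject may mean that the arms are alike, or only that the comparison is imprecise. Section 4.1.3 applies one testing approach to all the hypotheses without setting apart those that predict similarity.

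What is at stake is interpretation. The trial's account is that both programmes train people equally well at first and then diverge because PlayFit is better attended. If the arms already differ at month 6, part of a month-12 gap could come from a different training stimulus. Whether the month-6 data support near-equality is therefore worth stating properly. For injuries, a similar rate is part of the case that PlayFit is no less safe than the comparator, and the same logic applies.

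**Working it through.** **Inputs (Sample size determination, 4.1).** 112 per arm; SD 6.0 at both time points; correlation 0.39; two-sided 5% level; target difference 2.5; 112 × 1.25 = 140 per arm, 280 in total. Expected month-6 gain 3.5 in both arms.

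**Assumption.** The SD and correlation are given for two unnamed time points. I take them to apply from baseline to month 6.

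**Step 1: reproduce the plan's figure.**
- SD of change = √(6² + 6² − 2 × 0.39 × 6 × 6) = √43.92 = 6.627.
- n per arm = 2 × 43.92 × (1.96 + 0.8416)² / 2.5² = 110.3, so 111 by the normal approximation. The noncentral t gives 112, with power 80.3%.
- The stated 112 reproduces as a comparison of change scores.

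**Step 2: month-6 precision.** SE = SD × √(2/n), and the 95% half-width is 1.96 × SE. The baseline-adjusted SD is 6.0 × √(1 − 0.39²) = 5.525.

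| Basis | n per arm | SE | 95% half-width | 90% half-width |
|---|---|---|---|---|
| Change score | 112 | 0.886 | 1.74 | 1.46 |
| Change score | 140 | 0.792 | 1.55 | 1.30 |
| Baseline-adjusted | 112 | 0.738 | 1.45 | 1.21 |
| Baseline-adjusted | 140 | 0.660 | 1.29 | 1.09 |

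At 112 per arm, 1.74 is 50% of the expected gain (1.74/3.5) and 69% of the target difference (1.74/2.5). The adjusted 1.45 is 41% and 58%.

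**Step 3: how often would a real difference be non-significant?** The probability is Φ(1.96 − d/SE) − Φ(−1.96 − d/SE). The value d = 1.5 is illustrative and not from the article. At 112 per arm:
- Unadjusted: 1.5/0.886 = 1.694, giving 0.605 (0.608 by the noncentral t), about 61%.
- Adjusted: 1.5/0.738 = 2.032, giving 0.471, about 47%.
- For other unadjusted values: 80% at d = 1.0, 49% at 1.75 and 19% at 2.5.

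**Step 4: could similarity be shown with an interval?** If the arms are truly equal, the chance that the 90% interval lies inside ±m is 2Φ(m/SE − 1.645) − 1, or zero if that is negative. The article gives no margin, so both margins below are assumptions.

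| Margin | Unadjusted, 112 | Adjusted, 112 | Unadjusted, 140 | Adjusted, 140 |
|---|---|---|---|---|
| ±1.75 (half the expected gain) | 26% | 53% | 43% | 69% |
| ±2.5 (the target difference) | 76% | 92% | 87% | 97% |

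At 112 per arm, no margin below about 1.46 (unadjusted) or 1.21 (adjusted) could be met, since the interval itself is wider than that.

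**Injuries.** The article gives no expected rates, so no calculation is possible. The point there is logical only.

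**The case against.** The strongest reply is that nowhere does the article say a p-value above 0.05 will be read as similarity. A random regression model yields a month-6 estimate and interval, and the rule for reading it may sit in an analysis plan that is not shown. This stands as a limit. A reader might infer that the investigators have committed to that reading, but the text does not say so. What the article does fix is the pair of similarity hypotheses, the statement that hypotheses are tested by these models, and a sample size built only for a difference.

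Second, one might conclude that the trial's precision can never support similarity. That is too strong, because it depends on the margin. At ±2.5 the chance of success is 76% to 92% with 112 per arm. But 2.5 is the difference the trial itself is built to detect, so it would be an odd width for calling the arms alike.

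Third, month-6 equality appears in the sample size section only as an expectation, the trial is sized on month 12, and the adherence and enjoyment pathway has its own mediator analysis (4.1.5). This also stands. It would be wrong to infer that the month-12 comparison or the sample size fails. The Abstract and Overview nevertheless present equality at month 6 as a hypothesis in its own right.

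Finally, Section 2.1 sets the injury aim as examining group differences, which suits an estimate with an interval. Only the hypothesis of similar rates goes further.

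**Conclusion.** The concern holds in limited form. The article hypothesises similarity at month 6 and similar injury rates, while its stated testing approach and sample size are directed at differences. A non-significant month-6 result would be weak evidence. Its interval would extend about 1.74 ml/kg/min either side of the estimate (1.45 adjusted), and a true difference of 1.5 would go undetected about 61% of the time (47% adjusted).

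These figures rest on 112 per arm and on the stated SD and correlation applying to month 6. Which SD is closer depends on how the model handles baseline, which the article does not settle, so both are shown. The month-12 superiority comparison and its sample size are not affected. The change is worth making but is not critical.

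**What to change.** - In Section 4.1.3, state that similarity at month 6 will not be inferred from a non-significant test, and that the month-6 between-arm difference will be reported with its confidence interval.
- Claim similarity only if the 90% interval lies within a margin that the investigators justify in advance. If no margin is set, reword the Abstract and Overview so that month-6 similarity is an expectation, described by the estimate and interval.
- For injuries, report the between-arm rate difference by randomised group with its interval, and draw no conclusion of similar rates from a non-significant test. A rate per session attended can be a supplement only, because attendance arises after randomisation and is expected to differ between arms.

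The cost is a few sentences and one interval comparison, with no extra participants or data. The downside is that a similarity claim may not be reached. At an assumed margin of ±1.75, truly equal arms would meet it only 26% (unadjusted) to 53% (adjusted) of the time with 112 per arm, and 43% to 69% with 140.

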### Participants

2.2

#### Eligibility criteria

2.2.1

Participants will be healthy, but sedentary, adults between 18 and 50 years of age [29]. The participatns will be considered “sedentary” if they report fewer than 90-minutes of MVPA each week [30], based on questions provided in the International Physical Activity Questionnaire (IPAQ; [31]). Finally, because some participants who are screened will be at increased risk for heart disease (and others may have unrecognized symptoms [32]), a physician must provide clearance for participants who answer affirmatively to any item on the Physical Activity Readiness Questionnaire (PAR-Q; [33]). This clearance is particularly important as the proposed physical activities will be moderate-to vigorous-intensity [34].

#### Recruitment and screening

2.2.2

We will send recruitment letters to patients in the Penn State Health system who reside within a 10-mile radius of each exercise site. If our recruitment rate is unsatisfactory, we will also use a commercial mailing list provider, such as Lorton Data (Arden Hills, MN). To ensure eligibility and review the study procedures, trained research staff will screen individuals over the phone using a standardized script. Prior to enrollment and any study measures, eligible participants will attend a 60-minute orientation session led by trained research staff in a designated location near each exercise site. Similar orientation sessions have successfully improved retention in weight-loss trials by exposing potential participants to more information about the study and its expectations. The orientation session will include: 1) addressing the time and scheduling demands of enrolling and participating in a 12-month RCT (e.g., considering realizing the difficulty associated with travel to PA program sites/measurement sessions), 2) the barriers to PA change after having been chronically sedentary, overweight, and/or obese (e.g., soreness), and 3) managing expectations for individuals and groups (e.g., not being randomized to the group he or she was hoping to be) [35]. In addition, because commitment devices have been shown to positively influence habit formation [36], at the end of the orientation session, we will ask participants still interested in enrolling to make an informal commitment to attend at least 2 out of 4 exercise sessions per week, by viewing the schedule of available exercise sessions, and personally initialing the days that they intend to participate on a monthly basis. If the individual remains interested after the orientation session, he or she will schedule a baseline visit to sign the informed consent and collect initial measurements.

### Measures

2.3

#### Primary outcomes

2.3.1

**Cardiorespiratory fitness (VO**_**2peak**_**).** Cardiorespiratory fitness at baseline and month-6 and-12 will be assessed using a graded-exercise test (GXT). The GXT will be performed using a Bruce protocol [37] on a computerized treadmill while breath-by-breath data is collected using a two-way valve attached to a metabolic measurement system, such as Parvomedics (Salt Lake City, UT). Prior to each test, the system will be calibrated for oxygen and carbon dioxide using a certified mixture of the gases and for ventilation using a 3-l syringe and a standard 15-stroke calibration procedure. During each GXT, a clinical exercise physiologist will collect heart rate and blood pressure measurements, as well as monitor electrocardiography (ECG) data for adverse responses. The test will be terminated at the point of volitional exhaustion. We will consider VO_2peak_ as the point at which three or more of the following criteria are met: 1) a plateau in VO_2_ despite increasing running speed, 2) a respiratory exchange ratio (RER) higher than 1.1, 3) an inability to maintain the required velocity, or 4) heart rate above 90% of age-predicted maximum [38].

**Weekly moderate-to vigorous-intensity physical activity.** We will use tri-axial accelerometers (ActiGraph GT3X, Pensacola, FL) to measure ambulatory MVPA. The accelerometer will be worn for 7-days following each in-person exercise test visit (baseline, 6, 12-month). Research staff will ensure that participants understand how to correctly wear the accelerometer and will send daily reminders to wear the device during the accelerometer wear period. These data will be stored as 10-second epochs, based on regression equations determined by Crouter and colleagues [39], who tested a range of sports and exercises characterized by intermittent bursts of activity similar to the sports and exercises in PlayFit and STT. We will derive minutes-per-day that each participant spends in MVPA (>2,019 counts per minute) using the cut-points recommended by Matthew and colleagues [40]. Researchers using the ActiGraph and similar tri-axial accelerometers have reported excellent reliability among other adult samples [41,42]. We will inspect these data for quality assurance by requiring participants to provide at least 10-hours of waking wear time each day, use paper-and-pencil activity logs to determine non-wear periods, and require at least 5 valid days or 66 valid hours over 7-days and at least one weekend day of wearing the device [43].

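### Accelerometer non-wear is taken from participants' paper logs with no stated check against the stored signal, so days or weeks with too little real wear can be accepted as valid and lower mean MVPA

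*Protocol article*

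**What the plan says.** Section 2.3.1 (Primary outcomes, paragraph on weekly MVPA) has participants wear an ActiGraph GT3X for 7 days at baseline, 6 and 12 months. On the signal it says "These data will be stored as 10-second epochs". The outcome is minutes per day above a count threshold; no scaling to wear time is described.

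Three validity conditions follow. The day-level one is "requiring participants to provide at least 10-hours of waking wear time each day". The week-level ones are to "require at least 5 valid days or 66 valid hours over 7-days and at least one weekend day of wearing the device". Between them stands the only stated means of finding non-wear: staff will "use paper-and-pencil activity logs to determine non-wear periods".

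Staff will also explain how to wear the device and "will send daily reminders to wear the device during the accelerometer wear period". These reminders concern wearing; none is described for completing the log.

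**The concern.** All three validity conditions depend on wear time being known. With a self-completed log as the source, a removal that is not written down, or a log that is not returned, turns non-wear into apparent wear. The hours off the body appear as zero counts and are credited towards the 10-hour rule. A day that the rule should exclude then stays in the average with too few MVPA minutes, and a participant with too little wear can be kept as a valid week.

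Accelerometer MVPA is placed under Primary outcomes in section 2.3.1, and objectively monitored MVPA is part of the first aim in section 2.1. The stored epochs would already show most long removals, so the plan relies on the weaker of two sources that it will have.

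**Working it through.** The article gives no sample size, power or target difference for MVPA (section 4.1 covers only VO2peak), so there is no stated figure to reproduce. The check compares the two ways of finding non-wear, day by day.

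**From section 2.3.1:** 7 days of wear; a valid day needs at least 10 waking hours; a valid week needs 5 valid days or 66 valid hours, including a weekend day; the outcome is absolute minutes per day.

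**Assumed, because the article does not give them:** waking time W = 14 h (range 14 to 16); true MVPA M = 30 min on every day, spread evenly over waking hours; u hours of unlogged removal on k of the 7 days; all of that removal visible as zero counts.

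**Formulas**
- Recorded MVPA on an affected day = M × (W − u)/W.
- Log rule (all 7 days appear fully worn): mean = [(7 − k) × M + k × M × (W − u)/W]/7, a relative error of −k × u/(7 × W).
- Signal rule: an affected day is dropped if W − u < 10; otherwise it stays, with the same recorded minutes as under the log rule.

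**When the rules differ.** They differ only if u > W − 10, that is, more than 4 h of unlogged removal in one day at W = 14, 5 h at W = 15 and 6 h at W = 16.

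**Results at W = 14, M = 30**

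| u (h) | k (days) | Real wear on those days | Log rule, min/day | Signal rule |
|---|---|---|---|---|
| 4 | 2 | 10 h | 27.6 (−8.2%) | 27.6, 7 valid days |
| 5 | 2 | 9 h | 26.9 (−10.2%) | 30.0, 5 valid days |
| 8 | 2 | 6 h | 25.1 (−16.3%) | 30.0, 5 valid days |
| 8 | 3 | 6 h | 22.7 (−24.5%) | 4 valid days: week not valid |

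Second row in full: 30 × 9/14 = 19.29 on each short day; (5 × 30 + 2 × 19.29)/7 = 26.9; error = −(2 × 5)/(7 × 14) = −10.2%.

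The first row shows no difference, because real wear still reaches 10 h. In the last row the signal rule leaves 4 × 14 = 56 h on valid days (4 × 16 = 64 h if W = 16). Both are below 66 h, reading valid hours as hours on valid days, so the week becomes missing. The log rule would have kept it at 22.7 min/day.

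**Range.** With one or two short days, W from 14 to 16 h and up to 8 unlogged hours, the log-rule error runs from −5.1% (W = 14, u = 5, k = 1) to −16.3% (W = 14, u = 8, k = 2).

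**The case against.** The strongest objection is that most MVPA lost while the monitor is off is lost under either rule. The outcome is absolute minutes per day, so activity done unworn is not recovered by finding non-wear more accurately. A reader might infer that every unlogged removal, such as one around an evening session, is an error caused by the log. The documents do not support that: such a day would usually still have 10 h of real wear, count as valid either way and show the same minutes. A removal shorter than the chosen zero-count run would not be flagged at all. This stands, and it confines the point to short days and under-worn weeks.

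Second, the article says staff will inspect the data for quality, does not say that the log is the only source, and may leave scoring settings to a fuller document. This stands in part. The article does not show that the signal will be ignored, but it does name the log as the means of determining non-wear, and that is a stated choice. Nor does it describe a wear sensor; non-wear would have to be inferred from stored counts.

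Third, a reader might infer a bias between arms, because the trial expects adherence to differ by month 12 and section 3.1 describes blinding of staff only. The hypothesis concerns attendance and fitness. Nothing in the article links log-keeping to arm, and wear instructions and reminders are described without distinction by arm. A difference by arm is possible but not shown.

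Fourth, the powered outcome is VO2peak (section 4.1), section 4.1.1 puts the primary analysis on fitness, and the abstract's list of primary outcomes does not include MVPA. This stands and limits the consequence.

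**Conclusion.** The point holds in a narrow form. As written, section 2.3.1 allows a day with under 10 h of real wear, or a week below the 5-day or 66-hour rule, to be accepted when a long removal is not logged. Such days lower mean MVPA.

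In the illustration, two such days in a week cost 10% to 16% of that participant's mean at 14 waking hours. This rests on assumed waking time, even MVPA and assumed removal; how often long removals go unlogged is not given and could be rare. The 24.5% figure for three short days should not be read as bias that the fix would correct to 30.0 min/day, because that week would become missing.

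No stated figure changes, VO2peak is unaffected, and no bias in the comparison of arms is established. The change is still worth making, because it protects an outcome that section 2.3.1 lists as primary and uses data already collected.

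**What to change.** In section 2.3.1, define non-wear by a prespecified run of consecutive zero counts in the stored epochs, for example 60 minutes or more within waking hours. Apply it identically in both arms and at baseline, 6 and 12 months. Use the paper log to mark sleep and to corroborate the signal. Then apply the 10-hour, 5-day or 66-hour, and weekend-day conditions to the resulting wear time.

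The cost is a sentence or two and a scoring setting; no new data are needed. The downside is that some days, and some whole participant-weeks, that the log would have passed become invalid and therefore missing. Long still sitting may also occasionally be classed as non-wear. That removes no MVPA minutes from a day that stays valid, but it could push a borderline day below 10 h.
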